## Abstract

**Background:**

Decision-making tools represent a paradigm shift in the relationship between the clinician and the user/patient. Some of their advantages include patient commitment, the promotion of preferences and values, and increased treatment adherence.

This study protocol aims to assess the effectiveness of a decision-making tool in contraception (SHARECONTRACEPT) concerning: a) Improvement in counselling on hormonal contraception at the medical consultation, measured in terms of decreasing decisional conflict and improving knowledge of available contraceptive options; b) Improvement in adherence to treatment measured in terms of: persistence in the chosen treatment, compliance with dose or procedure of use, and ability to deal with incidents related to the use of the contraceptive method; and decreasing unwanted pregnancies and voluntary interruption of pregnancy.

The SHARECONTRACEPT tool, developed by previous phases of this project, is available at: http://decisionscompartides.gencat.cat/en/decidir-sobre/anticoncepcio_hormonal/

**Methods/design:**

A longitudinal, prospective-type, randomized, controlled community clinical trial, carried out in the clinical contraceptive counselling units of 6 autonomous regions in Spain, with an experimental group and a control group. Description of the intervention: The health professionals participating will be randomly assigned to one of the two groups. Clinicians assigned to the experimental group will perform contraceptive counselling assisted by SHARECONTRACEPT, and those of the control group will follow the conventional contraceptive counselling provided in their clinical unit.

It is planned to study 1708 users (control group *n* = 854 and intervention group *n* = 854), recruited from women who attend the consultations of the health professionals. The selected users will be followed up for one year. The data will be collected through ad-hoc questionnaires, and validated instruments for measuring decisional conflict and adherence to treatment.

**Discussion:**

The results of this study protocol will offer evidence of the effectiveness of a shared decision-making tool, SHARECONTRACEPT, which may prove a useful tool for users and professionals to promote adherence to contraceptive methods.

**Trial registration:**

Clinical Register number ISRCTN5827994. Date: 15/04/2019 (Retrospectively registered)

## Background

In Spain, nine out of ten women of childbearing age, between 15 and 49 years, report that they have had sex, at some time, and two out of ten report having had sex without using any method of contraception. In other words, some two million women would currently be exposed to an unwanted pregnancy in our country (SEC) [1]. In this regard, in 2015 a report was published that stated that approximately 35% of pregnancies in Spain were unwanted (some 190,000 unwanted pregnancies/year) [2].

Half of these unwanted pregnancies in Spain end in voluntary termination (VTP), 93,131 in 2016, according to a report on these terminations by the Spanish Ministry of Health. The report highlights a decline in VTPs in recent years and although it would be nice to think that this is due to better use of contraceptives, the fact that only 10.4% of total VTPs were due to medical reasons is worrying [3]. Also, it should not be forgotten that the role being played by emergency (post-coital) contraception to reduce unwanted pregnancies and the subsequent reduction in the rate of VTPs is not known; according to the latest survey of 2018, presented by the SEC, 30% of respondents reported resorting to emergency contraception, at some time [1].

The condom is the most popular form of contraceptive in Spain: it is used by 29.6% of the population, compared with 17.3% of women who use combined hormonal contraceptives (CHC), the most commonly used hormonal method of contraception across all age brackets. The population continues to rely, therefore, on the condom, a good way to avoid possible contagion by sexually transmitted diseases (STDs), but one that is not a very effective contraceptive in practice when compared with other hormonal methods due to its inconsistent and/or incorrect use [1]. Each year, eighteen out of every 100 women condom users get pregnant during their first year of use compared to nine out of 100 women users of CHC per year, according to Pearl indices corresponding to each method, as published recently by the World Health Organization (WHO) [4].

In the last 30 years, new hormonal contraceptives have been added to the range of existing contraceptive devices, drugs or technologies. Most of these additions have involved modifications or a variety of alternatives to oral hormonal contraception, the best-known and most widely used, but also to other methods such as the progestogen pill (used by 0.1%), combined injectable contraceptives (used by 0.2%), patches (used by 0.7%), and the combined hormonal vaginal ring (used by 2.9%). Long-acting reversible contraception (LARC) methods, including intrauterine devices (IUDs) and the subdermal implant, are the most effective as regards avoiding unwanted pregnancies (Pearl index for implants, the Levonorgestrel IUD and the copper IUD of 0.05, 0.2 and 0.8–2 pregnancies per 100 women/year, respectively) [5]. Based on the latest results of the SEC, in 2018, an increase can be seen in the last year in the use of LARC (9.6% of total users), with respect to the 2016 survey (7.7% of total users) [1, 6].

According to the results of the latest survey on the use of contraceptives in Spain, 1% used an implant, 4.3% had a hormonal IUD and 4.3% had a copper IUD [1]. These methods, in addition to their excellent cost-effectiveness ratio and comfort and safety for the health of women, are highly efficient as they do not influence non-compliance with or the misuse of the method by the user. This aspect differentiates them from other hormonal methods, which, while highly effective in theory, their effectiveness is reduced by the lack of adherence to treatment [1, 4, 7].

The term adherence includes two concepts: compliance with doses (taken correctly in accordance with the drug posology) and persistence in the duration of the prescribed treatment (constant use of treatment over time) [8]. The lack of adherence to contraceptive treatments generally compromises their effectiveness and results in many of the unwanted pregnancies and VTPs, with an estimated annual cost of approximately 80 million euros to the national health system [2].

In a recent review, it was found that in Spain, non-compliant use of contraceptives among users of CHC is common, between 65 and 70% of users forget or delay a pill more than once a month, but moreover, 18% did not use any additional method subsequently and 43% were distressed by the possibility of getting pregnant that month, showing a lack of skills and knowledge as to how to act in the event of an oversight or non-compliance [8]. In addition, there is a high dropout rate from CHC within 12 months of the start of treatment, with figures close to 50%, which are due to the onset of side effects and/or the lack of adherence to treatment [9].

The low use of LARC is not influenced by the lack of adherence, but could be explained by problems related to: a lack of knowledge of such methods, accessibility to them, and the bleeding pattern they present that is not accepted by all women, as they are not informed of it [1, 4, 5, 10]. In this regard, recent SEC survey data show that 45.6% of women acknowledged that their doctor or midwife did not offer them the contraceptive option of a LARC during their counselling consultation, despite the fact that in several of the autonomous communities participating in the population survey, this type of long-acting contraception is financed wholly or in part [1, 10].

The data set out above show the need to encourage the population of potential users of contraceptive methods to get access to balanced and objective information on the different contraceptive methods based on the latest scientific evidence to help them choose the most suitable to their health status and their personal situation [4]. Dehlendorf, the author of an interesting review of how contraceptive advice should be given, stresses the need for clinicians, before such demand, to establish a close and trusting relationship with users.

In recent years, the patient has acquired a more active and responsible role in relation to the management of their health and in the clinical practice. On a daily basis, patients and healthcare professionals face situations in which decisions related to the diagnostic process and/or different treatment options should be taken jointly [11, 12]. To facilitate this, shared decision-making tools (SDMT) have been developed, that promote discussion between patients and healthcare professionals concerning the various treatment options [11–13].

The purpose of this study protocol is to evaluate the effectiveness of an SDMT in open access online digital hormonal contraception during contraceptive counselling consultation, according to the needs of the population.

## Methods/design

### Study framework

The SDMT in hormonal contraception, SHARECONTRACEPT, was previously devised by the authors [name], [name] and [name].

In August 2018, it was published on the “Decisions Compartides” website of the Department of Health of the Generalitat (Government) of Catalonia, in Spanish, Catalan and English: http://decisionscompartides.gencat.cat/en/decidir-sobre/anticoncepcio_hormonal/index.html).

Below, we set out how it was produced, as we consider it relevant as a reference framework for the study:

For the design of the SHARECONTRACEPT SDMT, the criteria of the *International Patient Decision Aid Standards* (IPDAS), an international group of researchers and health professionals set up in 2003 to determine the standard criteria for the development of SDMT in view of their increasing occurrence, were followed [13, 14]. These criteria, grouped in a checklist of 30 items, establish the three blocks for inclusion in SDMTs: clinical content, development process and evaluation of effectiveness [13, 15].

For the SHARECONTRACEPT development process, the stages described by the National Health System (NHS) Agency for Evaluation, Technology and Performance were followed for SDMT evaluation and validation [15]. Then, the development process is described in stages (Study framework flowchart of the design of SHARECONTRACEPT, Fig. 1).

**Fig. 1 Fig1:**
[figure not shown]
Study framework of the development of the Shared Decision-Making Tool following the stages described by the National Health System (NHS) Agency for Evaluation, Technology and Performance

### Clinical trial of SHARECONTRACEPT

#### Hypothesis

Advice on hormonal contraception at the physician’s office, with the support of the SHARECONTRACEPT SDMT, encourages dialogue and the exchange of information between the woman and the clinician, which can help select a contraceptive method more in accordance with her preferences, needs, priorities and characteristics, thus improving adherence to the method of choice.

#### Aims and objectives

The purpose of this project is to evaluate the effectiveness of the SHARECONTRACEPT SDMT during contraceptive counselling in six autonomous communities of Spain
To determine whether the use of SHARECONTRACEPT *improves* adherence to the chosen contraceptive treatment, in relation to compliance with dose or method of use and persistence in the duration of the prescribed treatment,To assess whether SHARECONTRACEPT increases the ability to cope with incidents related to the use of the method,To assess the social impact of using SHARECONTRACEPT in relation to decreasing unwanted pregnancies and voluntary termination of pregnancy (VTP),To analyse whether SHARECONTRACEPT decreases the woman’s conflict in view of the choice of contraceptive method,To assess whether the use of SHARECONTRACEPT helps clinicians to better understand the various hormonal contraceptive options available and their characteristics (risks, benefits and consequences), and.To analyse whether the use of SHARECONTRACEPT changes the pattern of use of hormonal contraception in the population towards more effective methods.

#### Design

The research is approached as a longitudinal, prospective community clinical trial. While in the conventional format of clinical trials allocation is performed on the participating subjects themselves, in the community format, clusters are assigned to which the units of analysis belong.

In this research, the clusters are the professionals of the Clinical Units of the six participating Spanish autonomous communities: Madrid, Aragon, Galicia, the Basque Country, Valencia and Catalonia (see Fig. 2). The units of analysis are the women attending the consultation of the professionals between 1 July 2019 and 30 June 2020.

**Fig. 2 Fig2:**
[figure not shown]
Map of participating communities where the clusters were selected. Created by the author

### Clusters sample

Firstly, the clusters were selected. The researchers responsible for each of the six autonomous communities in Spain recruited them by means of convenience sampling. During the first quarter of 2019, professional clinicians giving contraceptive counselling (gynaecologists, midwives, family doctors and/or nurses) from the different Spanish autonomous communities participating were invited to take part. One hundred and sixty-four (164) professionals agreed to participate and they were randomly assigned using the EPIDAT program (single sampling), to one of two groups:
Experimental Group (EG), professionals who will perform counselling with the support of the SHARECONTRACEPT SDMT, andControl group (CG), professionals who will perform clinical counselling as they had until then (conventional contraceptive counselling).

Starting from this context, it was decided to create the Web page: Sharecontracept.com, through which the professionals can easily access the three different environments in which they are to participate.

#### 1-virtual campus

In order, insofar as possible, to standardize the procedure to be followed given that the different professional profiles and broad geographical spread, the Foundation of the Rovira i Virgili University in Tarragona (Spain) designed a 60-h online course for the professionals involved in the project.

This course is to be implemented prior to starting the fieldwork. There are two courses, one for the CG and the other for EG. The professionals of each group will receive an email with a link in order to access the corresponding SHARECONTRACEPT virtual course with a username and a password. Once inside the course, and after a brief presentation, they will be asked to perform a test of knowledge on contraception at the beginning and at the end of the course, to assess whether SHARECONTRACEPT improves the knowledge of the professionals who use it. After the first test, the system will allow them access to the rest of the course environment, where, among others, they will find forums through which they can contact the research team.

In addition, through documents and videos, they will get access to the contents of the different subjects (see Table 1), depending on whether they are professionals assigned to EG (they will be able to view the six subjects from the beginning) or CG (during the fieldwork they will only be able to view subjects 2 and 6, although they will be able to get access to the rest once sample collection has finished).

**Table 1 Tab1:** Moodle course table of contents

Theme 1	The shared decisions model
Theme 2	The SHARECONTRACEPT project
Theme 3	Which are the WHO’s eligibility criteria
Theme 4	Keys to giving good counselling
Theme 5	Videos with examples of how to counsel with the support of SHARECONTRACEPT
Theme 6	Instructions on how to implement the information collection platform of the SHARECONTRACEPT Project

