##### Information collection questionnaires

Information on each of the women will be collected at four times during a year, from two online questionnaires developed ad hoc: an in-person survey and a telephone survey (to be conducted 3 times: at one month, at 6 months, and one year following the in-person consultation).

The main variable is adherence to treatment (compliance with the dose and method of administration and persistence in the duration of the prescribed treatment) and the secondary variables include *the woman’s sociodemographic characteristics, her medical, obstetrical and gynaecological history, her contraceptive method, decisional conflict, and variables of the professional* (see Table 3).

**Table 3 Tab3:** Variables collected in the study

Main variable	*Adherence to treatment:*
	• Compliance with dose and method of administration and
	• Persistence in the duration of the prescribed treatment
Secondary variables	*Woman’s sociodemographic characteristics:*
	• Age
	• Level of education
	• Occupation
	• Marital status/partner
	*Contact details*
	*• Telephone*
	*• Telephone 2*
	*Medical history:*
	*•* Smoker
	*•* HBP
	*•* Uterine malformations
	*Obstetric and gynaecological history:*
	*•* Menstrual pattern
	*•* Miscarriage
	*•* VTP
	*•* Living children
	*Contraceptive method*
	*•* Contraceptive method considered by the patient before counselling
	*•* Experiences with other methods
	*•* Woman’s attitude towards compliance (Morisky-Green treatment adherence test)
	*•* Contraceptive finally chosen
	*•* Incidents with the chosen method
	*•* Incident management
	Decisional conflict
	The woman’s decisional conflict in view of the choice of contraceptive method (O’Connor Scale) https://decisionaid.ohri.ca/eval_dcs.html
	And of the professional:
	*•* Satisfaction with the counsellor or clinician with the use of the digital SDMT (Likert scale)
	*•* Test of knowledge prior to and after fieldwork

**The statistical approach** will consist of a set of bivariate and multivariate descriptive analyses and the application of logistic regression models to determine the extent to which the likelihood of changing birth control method and the likelihood of choosing one particular method are linked to certain specified variables. Losses are considered as women that do not complete the follow-up of the protocol to which they were assigned or that do not to remain until the end of the analysis.

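### The professionals' second knowledge test is dated two ways, one of them before any study use of SHARECONTRACEPT, and the arm-specific training means effects belong to the tool-plus-training package rather than the tool alone

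*Protocol article*

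**What the plan says.** All references are to the protocol article.

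**Timing of the knowledge test.** Under 1-virtual campus, professionals in both groups take "a test of knowledge on contraception at the beginning and at the end of the course", and the purpose is "to assess whether SHARECONTRACEPT improves the knowledge of the professionals who use it". The same section says: "This course is to be implemented prior to starting the fieldwork". The next two sections (2- user registration and 3-platform) have professionals register after going through the course material and only then start entering cases. Table 3, among the variables of the professional, gives the schedule as "Test of knowledge prior to and after fieldwork". Under Design, the women attend "between 1 July 2019 and 30 June 2020".

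**Course content.** Experimental-group (EG) professionals see all six themes of Table 1 from the start. Control-group (CG) professionals see only Theme 2 (the project) and Theme 6 (the data platform) while fieldwork runs. The other four open to them when sample collection is over. Those four are Theme 1 (the shared-decision model), Theme 3 (the WHO eligibility criteria), Theme 4 ("Keys to giving good counselling") and Theme 5 (videos on counselling with the tool).

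**What the effects are credited to.** The knowledge objective is "To assess whether the use of SHARECONTRACEPT helps clinicians to better understand the various hormonal contraceptive options available". The adherence objective likewise looks to the tool for a gain in "adherence to the chosen contraceptive treatment, in relation to compliance with dose or method of use and persistence in the duration of the prescribed treatment". Clusters sample defines EG by counselling with the tool and CG by counselling as before. The training is not named as part of the intervention.

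**The concern.** There are two linked problems.

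First, a test at the end of a course that precedes fieldwork cannot show what using the tool does, because no professional has yet used it in the study. It shows what the course taught, and the course differs by arm. Whoever follows the course section and whoever follows Table 3 would report different quantities under the same objective.

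Second, training is assigned together with the arm, so randomisation does not separate it from the tool. The article itself makes training a credible cause of better outcomes: its Discussion says clinicians' knowledge of contraceptive methods can be inaccurate or out of date, and that what clinicians mention or recommend weighs heavily on women's choices. Study limitations lists professionals' differing levels of training, but not the training difference that the design itself creates.

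At stake is the meaning of the knowledge result, and whether a positive result on adherence or decisional conflict is reported as the effect of an online tool or of the tool plus a course.

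**Working it through.** No stated figure bears on this point. The sample-size figure of 854 per group does not enter it. The check is a comparison of the article's own statements.

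**Step 1: can the two schedules be the same?**

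| | First test | Second test |
|---|---|---|
| 1-virtual campus | start of course, before fieldwork | end of course, with the course placed before fieldwork |
| Table 3 | before fieldwork | after fieldwork |

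The first tests are compatible. Taking fieldwork to begin with the recruitment window, the second test falls no later than about 1 July 2019 on one schedule and no earlier than 30 June 2020 on the other. That is a gap of at least 12 months, the whole period in which the tool is used in study consultations.

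**Step 2: what differs between the arms during fieldwork?**

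- EG themes: 1, 2, 3, 4, 5, 6 (six).
- CG themes: 2, 6 (two).
- EG only: 6 − 2 = 4 themes (1, 3, 4, 5).
- Of these four, Themes 1 and 5 can fairly be seen as instruction in delivering the tool. Themes 3 and 4 (two of four) appear from their titles to be general teaching.
- Judged by title, neither CG theme covers contraception.

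**Step 3: what would the between-arm difference at the second test contain?**

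| Second test taken | Study use of the tool in EG | Withheld themes seen by CG | What the difference reflects |
|---|---|---|---|
| End of a course completed before fieldwork | none | no | course content only |
| After fieldwork, before the withheld themes open | yes | no | tool plus training versus neither |
| After fieldwork, after the withheld themes open | yes | yes | as the row above, but with CG also taught |

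Only the second row gives a clean contrast for the randomised package. The course section points to the first row. Table 3 allows the second or the third, because the article uses the end of fieldwork and the end of sample collection as the same limit for CG's restricted view and does not say whether the test or the opening of the themes comes first.

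**Step 4: does the same hold for adherence and decisional conflict?** These are measured in women counselled during fieldwork, when EG has the tool and six themes and CG has neither the tool nor the four withheld themes. The contrast is unconfounded for the package. There is no arm with the training but not the tool, or the tool but not the training, so the package effect cannot be split.

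**The case against.** The strongest reply on timing is that a course placed before fieldwork may mean a course launched, not finished, by then. The course environment does continue: it hosts forums, limits CG's view while fieldwork runs, and opens the rest later. If its end falls after fieldwork, the two schedules agree, and the test fits its purpose of assessing professionals who use the tool. This reading is possible but strained, since the article also has the content reviewed before registration and case entry. Even if it is accepted, CG's second test still has no stated order relative to the opening of the withheld themes, so a clarification is needed either way.

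On attribution, several replies stand. Professionals are randomised, so the comparison is valid for the intervention as delivered. Training is a normal part of delivering a decision aid, and the article discloses the arm-specific course openly. Withholding counselling instruction from CG also protects the usual-care comparator. That Themes 3 and 4 do not depend on the tool is inferred from one-line titles, because the course content is not shown. Professionals' knowledge is a secondary variable, and the exact model for it can be left to a SAP. None of this justifies wording the objectives as effects of the tool with no mention of the training.

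A reader might go further and infer that no gain in knowledge or adherence can be credited to the intervention at all. The documents do not support that: the package comparison is sound.

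**Conclusion.** The point holds in two parts.

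1. The second knowledge test is dated inconsistently. Followed as written, the course schedule cannot address the knowledge objective, because it precedes study use of the tool and compares arms given six themes and two. This rests on reading the course as completed before cases are entered, which the order of the sections supports but does not state outright. No study use does not mean no possible exposure: the tool has been public since August 2018.

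2. Effects on adherence, decisional conflict and knowledge can be credited to SHARECONTRACEPT with its EG training, not to the tool separately from that training. The size can be stated only structurally: four of six themes differ by arm, two of them apparently general.

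A reader might infer that training could explain anything from none to all of an observed effect and treat that as an estimate. It is not one. It restates that the design cannot identify the split, and nothing in the article supplies a figure. Nor does the article propose making the website available on its own. It says only that the tool may prove useful.

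This should be corrected, but it does not undermine the trial's main randomised comparison.

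**What to change.** - Make 1-virtual campus and Table 3 agree: the same test for both arms at course start and at end of fieldwork, with CG tested before it is given Themes 1, 3, 4 and 5. Keep an end-of-course test only as a measure of the course.
- Base the knowledge objective on the between-arm difference at end of fieldwork, adjusted for the first score.
- Word the purpose, objectives and conclusion as the effect of SHARECONTRACEPT with its EG training versus conventional counselling, and name the training in the definition of the experimental group.
- Leave CG's course content as it is. Giving CG Themes 3 and 4 would narrow the contrast towards the tool, but would also change the usual-care comparator.

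The cost is one more run of an existing online test among the 164 professionals, plus changes of wording. The downside is that the trial's claim becomes one about the package rather than the tool alone.

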##### Sample selection criteria

The sample will be selected from the women attending the practice of one of the professionals from either CG or EG requesting counselling on contraception or when such need is found during the stipulated period (1 July 2019 to 30 June 2020) and who fulfil the following **inclusion criteria**: have completed their primary education and be competent in Spanish and/or Catalan (the languages of SHARECONTRACEPT, although it is also in English); be between 16 and 49 years of age, have internet access, and agree to participate voluntarily in the study. **Women are excluded** who wish to have children within one year of the date of consultation or have a history of: stroke, acute myocardial infarction, thrombosis, breast cancer (< 5 years), liver cirrhosis or liver tumour.

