## Data Availability

The study is ongoing. Data will be available when the study ends (31/12/2021).

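### Control professionals may open the experimental course themes when sample collection ends, which on its natural reading comes before every control woman's 12-month survey and risks late contamination of the control arm

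*Protocol article*

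**What the plan says.** The protocol article, under 1-virtual campus, describes separate online courses for the two groups. Experimental professionals see all six themes from the start. Of control professionals it says that "during the fieldwork they will only be able to view subjects 2 and 6". The same sentence then sets the point at which this restriction ends: "although they will be able to get access to the rest once sample collection has finished". By Table 1, the withheld themes are 1 (the shared-decisions model), 3 (WHO eligibility criteria), 4 (keys to counselling) and 5 (videos demonstrating counselling with the tool). Neither fieldwork nor sample collection is defined or dated.

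Under Sample selection criteria, women enter if they ask for contraceptive counselling or "when such need is found during the stipulated period (1 July 2019 to 30 June 2020"). Under Information collection questionnaires, data come from "an in-person survey and a telephone survey (to be conducted 3 times"), the calls being "at one month, at 6 months, and one year following the in-person consultation". The main variable is adherence, made up of compliance and persistence. Incidents and their management are also recorded, and Table 3 lists a knowledge test of the professionals before and after fieldwork.

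Under Study limitations, the plan recognises that control professionals might change their behaviour if they learn of the tool. Its only safeguard is to ask experimental professionals for confidentiality.

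**The concern.** The lock exists to keep control counselling conventional. If it lifts when recruitment closes, the teaching that it withholds becomes available to control professionals while all their enrolled women are still under follow-up. The outcomes at stake build up over that follow-up: whether a woman keeps to her method, uses it correctly and copes with incidents. A control woman who returns with a side effect, a missed dose or a wish to change could then be advised by someone who has watched the demonstration videos. If the tool works, this narrows the difference between arms.

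The knowledge comparison between professionals is exposed more directly, because it needs no return visit. If control professionals sit the final test after opening the themes, their score no longer reflects the control condition. The article does not settle the order: 1-virtual campus puts the second test at the end of the course, and Table 3 puts it after fieldwork.

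**Working it through.** **1. Which date does the milestone mean?**
- Under Sample size and Sample selection criteria, the sample is the women enrolled, and enrolment runs "during the stipulated period (1 July 2019 to 30 June 2020").
- The surveys go by another name: the heading is Information collection questionnaires, and Theme 6 refers to an information collection platform.
- So the end of sample collection most naturally means the end of recruitment, 30 June 2020.
- The other reading takes fieldwork, in the same sentence, to include the telephone surveys. The lock then lasts to about 30 June 2021.

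**2. What is outstanding on 30 June 2020?** Inputs: 366 enrolment days (1 July 2019 to 30 June 2020), calls at 1, 6 and 12 months, and 854 control women (Table 2). Even accrual is an assumption. A call is outstanding if enrolment date plus 1, 6 or 12 months falls after 30 June 2020.

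| Call | Enrolment days with call outstanding | Share | Control women |
|---|---|---|---|
| 1 month | 30 of 366 (enrolled in June 2020) | 8.2% | 854 × 30/366 = 70 |
| 6 months | 182 of 366 (enrolled from 1 January 2020) | 49.7% | 854 × 182/366 = 425 |
| 12 months | 366 of 366 | 100% | 854 |

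The 12-month calls run from 1 July 2020 to 30 June 2021. Follow-up after release therefore ranges from one day for the first woman to 12 months for the last. Averaged over enrolment days, it is 50% of the follow-up year. The 12-month row does not depend on even accrual. On the alternative reading every entry is zero.

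**3. Can the bias be sized?** No. That would need the share of control professionals who open the themes, the share of their women who return to them, the share of those visits in which counselling changes, and the outcome rates. The article gives none of these. It does not state the two proportions behind its sample size either, so 1,708 cannot be reproduced. Only the loss correction can be traced: 640/(1 − 0.25) = 853.3, rounded up to 854 per arm.

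**4. Illustration of sensitivity, on assumed rates.** Take 50% adherence in controls, 58% in the experimental arm and 640 evaluable per arm, ignoring clustering and the continuity correction. If a fraction f of the effect leaks to controls, the control rate is p₁ = 0.50 + 0.08f, p₂ stays at 0.58, and Δ = 0.08(1 − f). With p̄ the mean of the two rates,

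power = Φ{[Δ − 1.96√(2p̄(1 − p̄)/n)] / √([p₁(1 − p₁) + p₂(1 − p₂)]/n)}.

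For f = 0: (0.0800 − 0.0546)/0.0278 = 0.91, giving 82%.

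| f | Δ (points) | Power |
|---|---|---|
| 0 | 8.0 | 82% |
| 0.05 | 7.6 | 78% |
| 0.10 | 7.2 | 73.5% |
| 0.20 | 6.4 | 63% |

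This shows how power would respond to a given leak. It does not estimate the leak.

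**The case against.** The strongest reply is that the sentence can be read with no overlap. Elsewhere the article tends to say that women are recruited or selected and that information is collected, and it says that information is collected over a year. If fieldwork covers the calls, the lock already does what is wanted. The full protocol may also hold an exact unlock date. This reading is possible, and it makes the concern conditional. It does not remove it, because the sentence as written gives a release point that most naturally means the close of recruitment.

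A reader might go further and infer that the control arm crosses over. The documents do not support that:
- The randomised contrast is the counselling given at the consultation, which every enrolled control woman has already had in its conventional form. Her initial method choice, and her decisional conflict over it, are not affected.
- Control professionals may open the themes. Nothing says that they must, or that they then counsel with the tool.
- No repeat counselling is described. Follow-up is by telephone survey.
- The tool itself has been open online since August 2018. The lock withholds training in its use, not the tool.

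A reader might also take the Background statement that "there is a high dropout rate from CHC within 12 months of the start of treatment, with figures close to 50" per cent to mean that many control women would be re-counselled after release. That passage reports stopping, not returning. A woman who has already stopped has had her non-persistence event, and later advice cannot undo it. For persistence, only contact before stopping matters, and the article gives no rate for that.

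All these limits stand. They reduce the likely size of the problem and rule out a crossover, but they do not rule out late contamination.

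**Conclusion.** The point holds as an avoidable risk of late control contamination, and the remedy is a cheap improvement. On the natural reading, release on 30 June 2020 precedes the 12-month survey of all control women and, with even accrual, the 6-month survey of about 50% and the 1-month survey of about 8%. For women who return to their professional, 6- and 12-month compliance, persistence and incident handling could be biased towards no difference, assuming that the tool has an effect. The control professionals' final knowledge test is affected if it follows release. The size cannot be computed from the document and may be small. If fieldwork includes the telephone surveys there is no overlap, and the change below only makes that explicit.

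**What to change.** Under 1-virtual campus, replace the release milestone with: *once the last enrolled woman has completed her one-year telephone survey and the control professionals have taken their final knowledge test*. Keep Themes 1, 3, 4 and 5 locked for control accounts until then. The survey condition is met about 30 June 2021, six months before the study end given under Data Availability ("Data will be available when the study ends (31/12/2021").

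The cost is one sentence and one unlock date on the course platform. Control professionals would wait up to 12 months longer for the training. No extra women, visits or staff are needed.
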